## Study Objectives

This study will evaluate the efficacy of 6 months of HELP e-intervention access with kinesiologist support in a randomized controlled trial to determine if the changes in emotional health (primary outcome) and lifestyle behaviours (secondary outcomes) differ from changes among youth with delayed intervention access (control condition). Sustainability of the intervention will be assessed for an additional 6 months. Participants will be youth 12-17 years of age who contact youth mental health services (1Call1Click). We will also evaluate the impact of the HELP e-intervention on the use of mental healthcare services, the need for mental health professional support of lifestyle behaviours and the association between self-reported and objectively measured lifestyle behaviours.

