### Research Questions

1. Do youth (12 to 17 years of age) who engage in the 6-month HELP e-intervention have a larger improvement in emotional health (measured by the Strengths and Difficulties Questionnaire) than youth who do not receive the intervention?
2. Does engagement in the HELP e-intervention improve lifestyle behaviour (physical activity, sleep or screen time)?
3. Are changes in emotional health and lifestyle behaviours sustained for at least 6 months after completion of the HELP e-intervention?
4. Do youth who engage in the 6-month HELP e-intervention utilize fewer mental healthcare resources, during and for 1 year following RCT participation, than youth who do not receive the intervention?
5. Do mental health professionals supporting youth who engage in the 6-month HELP e-intervention provide lifestyle behaviour support less frequently than for youth who do not receive the intervention?
6. Are self-reported (i.e., perceived) lifestyle behaviour changes (study questionnaire responses) aligned with objective measures of screen time (smartphone tracking) and sleep and physical activity (accelerometry) in a randomly selected sub-sample (1 of 3) enrolled participants?

We hypothesize that youth engaging in the HELP e-intervention will have improved emotional health and enhanced lifestyle behaviours in comparison to those receiving the delayed (post 6-months) intervention. We hypothesize that changes during the intervention will be maintained for an additional 6 months, and that self-reported measures will accurately reflect objective measurements. We hypothesize that youth engaging in the HELP e-intervention will require fewer youth mental health supports, and when supported will be less likely to require treatment directed at lifestyle behaviours.

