# Study Design

This research will investigate the patient and healthcare system impacts of the HEalthy Lifestyle Project (HELP) e-intervention. The research design is a randomized, controlled trial comparing youth who immediately receive the intervention to youth randomized to receive the intervention 6-months later (wait list control). Efficacy outcomes will be assessed at 0, 3, 6 and 12 months. Healthcare system impacts will be extracted from medical records from 0 to 18 months.

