### Study Assessments

A researcher blinded to study group allocation will work with enrolled youth to complete all study assessments. The accurate/reliable study questionnaires include measures of emotional strength (Strengths and Difficulties Questionnaire)^34^, lifestyle choices (Youth Quality of Life-short form)^35^, readiness for behaviour change (Stages of Change Questionnaire^36^), and sleep (Adolescent Sleep Hygiene Scale)^37^, physical activity (Habitual Activity Estimation Scale)^38^, and leisure screen time (Adolescent Sedentary Activity Questionnaire)^39^ behaviours. All enrolled youth will complete all questionnaires at 0, 3, 6 and 12 months. As in our pilot study (REB #21 85X), the questionnaires (Appendix E) will be completed virtually using RedCAP, with automated scoring of the responses according to published methods. At each assessment, youth will be asked to voluntarily self-report age (years), gender (boy, girl, unkown, other, prefer not to answer), and their use of other mental health therapies (Appendix F). Study enrollment does not restrict access to or use of other mental health supports.

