The blinded researcher will also administer the objective measures of sleep, physical activity and lifestyle to a randomly selected sub-sample of participants. One in every three participants will be provided by mail with an accelerometer to wear for 7 days at the time of the 0 and 6-month assessments. Each selected youth will wear a tri-axial accelerometer (Actigraph GT9X-BT, 180 day memory) on a waist-worn belt, over the right hip, in the mid axillary line, 24 hours/day for 7 days^40^ in addition to completing the study questionnaires. The goal is 24 hour accelerometer wear for 7 consecutive days to capture both physical activity and sleep, and to minimize data loss (monitor forgotten, etc.). The Actigraph GT9X-BT ([www.theactigraph.com](http://www.theactigraph.com)) can be worn for swimming or bathing to a 1-metre depth. Sleep times and reasons for device removal will be recorded on a log sheet (Appendix G). A minimum of 10 hours of wear time per day during waking hours will be required so that established cut points^41^ can be used to calculate daily minutes of sedentary, light and moderate+vigorous activity. The ActiLife software (Version 6.13.5, Actigraph Inc.) also calculates sleep duration based on measurement epochs lacking movement. At least 3 weekdays and 1 weekend day of valid data will be required. Screen use will be measured by utilizing the social media tracking function in the smartphone owned by each participant^42^. The researcher will explain to each participant how to access the social media tracking function that is build into their smartphone. Participants will be asked to take a screen shot of their social media use each day at the time they go to bed and to share the screen shot with the research team. Participants who do not own a smartphone will not complete the objective measures of lifestyle behaviours.

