### HELP E-Intervention

All study participants will have access to the HELP e-intervention either immediately (HELP access between 0 and 6 months) or after a wait of 6 months (control condition, access between 6 and 12 months). The use of a wait list control is expected to decrease the impact of randomization on study recruitment and retention. Our unique HELP e-resources utilize age-appropriate graphics and interactive formats developed collaboratively with youth/parent/clinician partners. There are 4 sections: 1) Know Your Habits, 2) Physical Activity, 3) Screen Time, 4) Sleep. Know Your Habits provides youth with their personal baseline questionnaire results. Messages are tailored to each youth’s readiness for behaviour change and assessment results. Each behaviour section (physical activity, screen time, sleep) has 4 sub-sections. “Learn” conveys information linking the behaviour and youth mental health and targets youth not yet contemplating behaviour change. “Pros and Cons” targets ambivalence, supporting youth to consider the barriers/facilitators of behaviour change. “Goals” guides youth to choose from >70 step-by-step change plans. Each plan contains a sequence of 6-8 steps that youth complete to achieve their goal. Steps vary in required time (2-30 mins) and youth proceed through the steps at their preferred pace. SMART goal, overcoming road blocks and additional kinesiologist support resources are also provided. Youth can track their goals and accomplishments on the website. Access to all HELP e-modules is available to all youth but the website suggests individualized avenues for change based on each participant’s assessment results. Sample pages from the HELP e-intervention are provided in Appendix H.

Each participant will have a unique login to the HELP e-intervention (found at www.cheoactive.ca). By automatically tracking e-resource use (site visits, interactivity use, knowledge component completion), the website provides data regarding participant engagement with the intervention. These data also assess the frequency or type of e-resource use, important considerations in analyzing the intervention impact on behaviour change. Comparing initial and post-intervention questionnaire responses will indicate the potential emotional health/lifestyle behaviour change impacts of HELP e-resource access.

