Secondary efficacy outcomes are measures of readiness for behaviour change (i.e., stage of change) and sleep, physical activity and screen time behaviour. Behaviour change theory emphasizes that individuals move through a series of stages, with the most effective intervention differing for each stage. HELP supports youth in all stages of change. “Learn” targets youth not yet considering behaviour change. “Pro’s and Con’s” guides youth to address their ambivalence towards change. “Goals” provide step-by-step plans so youth can act on their intention to change behaviour. “Roadblocks” support the maintenance of recent behaviour changes. Paired t-tests will examine participants’ stage of change at enrollment and 6 months to assess whether HELP enhanced their readiness for behaviour change. Modeling how the behaviour change stage differs, with adjustments for age, gender, intervention adherence, type of mental health concern and support referral, will assess whether HELP similarly impacts behaviour change among all youth. The same analyses will be completed for each behaviour outcome with stage of change at 6-months a mandatory variable as theory indicates that achieving Stages 3 to 5 is required for behaviour change to occur (Stages 1 & 2 are moving toward the decision to change behaviour).

A repeated measures model of the primary and secondary outcomes will evaluate changes between study groups, comparing changes occurring during intervention access to changes when the intervention is not available. Changes between the 0 and 6-month assessments for youth randomized to immediate intervention access and between the 6 and 12-month assessments for youth randomized to the wait list group will evaluate HELP e-intervention efficacy. Differences between the 6 and 12-month assessments for youth randomized to immediate intervention access will evaluate the sustainability of the intervention effects. Differences between the 0 and 6-month assessments for youth randomized to the wait list group will evaluate changes in study outcomes over time without the HELP e-intervention. Comparisons between 0 and 3-month and 3 and 6-month outcomes will determine the required length of the HELP e-intervention for optimal outcomes. All models will be adjusted for age, gender, intervention adherence, type of mental health concern and support referral.

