### Study data

The data collection tools are the standardized questionnaires administered to assess intervention efficacy. Specifically, they are the measures of emotional strength (Strengths and Difficulties Questionnaire)^34^, lifestyle choices (Youth Quality of Life-short form)^35^, readiness for behaviour change (Stages of Change Questionnaire^36^), and sleep (Adolescent Sleep Hygiene Scale)^37^, physical activity (Habitual Activity Estimation Scale)^38^, and leisure screen time (Adolescent Sedentary Activity Questionnaire)^39^ behaviour. At each study assessment timepoint, participant’s self-reported age and gender will be recorded in RedCap, sample format is attached (Appendix F). The kinesiology support contact form (Appendix I) will standardize notes summarizing each support session or assessment delivered by a researcher. The retrospective collection of data from the medical records to analyze the healthcare system impacts will be completed using a RedCAP database (Appendix L).

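### Lifestyle efficacy is read from questionnaires by youth who will know their arm, while the only stated use of the objective measures is alignment with self-report, so over-reporting that differs by arm could go undetected

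*Protocol*

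**What the plan says.** **Efficacy instruments.** The protocol's Study data section says "The data collection tools are the standardized questionnaires administered to assess intervention efficacy" and then lists only questionnaires, among them those for sleep, activity and leisure screen time. The HELP E-Intervention section agrees: "Comparing initial and post-intervention questionnaire responses will indicate the potential emotional health/lifestyle behaviour change impacts of HELP e-resource access". The Efficacy Outcomes section states "Secondary efficacy outcomes are measures of readiness for behaviour change (i.e., stage of change) and sleep, physical activity and screen time behaviour", without naming an instrument.

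**Blinding.** Study Assessments says "A researcher blinded to study group allocation will work with enrolled youth to complete all study assessments". No blinding of participants is described. The Study Design section describes "comparing youth who immediately receive the intervention to youth randomized to receive the intervention 6-months later (wait list control"). HELP youth see their own baseline results, choose goals on these behaviours, and have staff contact 2-3 times a week at first and regularly for 6 months.

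**Objective measures.** Study Assessments says "One in every three participants will be provided by mail with an accelerometer to wear for 7 days", at months 0 and 6, with daily phone screenshots of social media use. Selection is not limited to one arm. The purpose given in Study Objectives is "the association between self-reported and objectively measured lifestyle behaviours", repeated as research question 6: "Are self-reported (i.e., perceived) lifestyle behaviour changes (study questionnaire responses) aligned with objective measures of screen time (smartphone tracking"). The protocol also hypothesises that self-report will match the objective data. The Data Analyses section names no objective measure and no arm comparison of one.

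**The concern.** The threat to research question 2 (does HELP improve lifestyle behaviour?) is not misreporting as such. Misreporting of equal size in both arms cancels from the arm comparison. The threat is misreporting that differs by arm, and this design makes that plausible: one arm receives a login, goals and coaching on the very behaviours it later reports, and the other waits. The Potential Risks section itself expects some youth to feel that their lifestyle answers will be judged.

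Overall alignment between self-report and device is a weak check on this threat. A constant shift in one arm leaves the ranking within each arm untouched, so the correlation scarcely moves. The trial could report good alignment and a HELP effect on behaviour when only reporting had changed. The measures that could show otherwise are planned in both arms over exactly the randomised window.

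**Working it through.** The protocol gives no figure for reporting bias or for the variability of behaviour change, so there is no stated number to reproduce. What follows illustrates size under labelled assumptions.

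**Inputs from the protocol.** 122 youth with complete data (Sample Size Determination); one in three measured objectively (Study Assessments); significance at 0.05 (Data Analyses).

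**Assumed.** 1:1 allocation and two-sided tests (neither is stated), so 122/2 = 61 per arm, and 122/3 = 40.7 measured, or about 20 per arm. True change has SD 20 min/day, reporting noise has SD 20 min/day, and there is no true HELP effect. HELP youth over-report by b more than controls. For scale only, the pilot activity change was 26 min/day (Summary of Work to Date), in a cohort of 6 youth, 5 with complete data.

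**Step 1: false effect on self-report.** SD of self-reported change = √(20² + 20²) = 28.3. The apparent standardised effect is b/28.3: 0.35 for b = 10 and 0.53 for b = 15. The rejection rates below come from simulated t-tests.

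**Step 2: overall correlation.** With half the youth in each arm, the shift adds b²/4 to the variance of self-report, so r = 20/√(800 + b²/4). For b = 0: 20/28.28 = 0.71. For b = 10: 20/√825 = 0.70. For b = 15: 20/√856.25 = 0.68. Simulated means in a 40-youth sub-sample are slightly lower.

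**Step 3: discrepancy (self-report change minus accelerometer change) compared by arm.** Its SD is the reporting noise, 20. With 20 per arm the standardised differences are 10/20 = 0.50 and 15/20 = 0.75.

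| Extra over-report, b (min/day) | Self-report test significant, 61 per arm | Mean overall r, sub-sample | By-arm discrepancy test significant, 20 per arm |
|---|---|---|---|
| 5 | 17% | 0.70 | 12% |
| 10 | 49% | 0.69 | 35% |
| 15 | 82% | 0.68 | 63% |

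**Step 4: the same on a standardised scale.** With no true effect and 61 per arm, biases of 0.2, 0.3, 0.4 and 0.5 SD give a significant self-report effect in about 20%, 38%, 60% and 79% of trials. With a within-arm correlation of 0.60, a 0.5 SD bias lowers the overall correlation only to 0.58. An overall mean difference would show 0.25 SD, half the bias, and could not assign it to an arm. Split by arm it is 0 against 0.5 SD.

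**Step 5: what an arm comparison of the objective data can detect.** At 20 per arm and 80% power, d = 0.91 (t-test). Across the expected enrolment of 100 to 200, about 33 to 67 youth are measured, 17 to 33 per arm. By the normal approximation the detectable d is 0.97 to 0.69, and power for d = 0.5 is 30% to 53%. If 20% were lost to invalid wear or lack of a smartphone (assumed), leaving 16 per arm, detectable d is 1.02 and power for d = 0.5 is 28%.

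**Step 6: why the discrepancy must stay in minutes.** Suppose HELP truly adds 26 min/day and there is no reporting bias. Standardising each measure by its own within-arm SD gives 26/28.3 − 26/20 = 0.92 − 1.30 = −0.38 SD. In simulation at 20 per arm, that test rejects in about 36% of trials. It would signal under-reporting where there is none.

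**The case against.** The strongest reply is that the protocol does not fix a pooled analysis. Question 6 names a sample, not a statistic, and a split by arm is something a statistical analysis plan could supply. That stands: a reader might infer that the protocol rules out an arm split or prescribes a single overall correlation, and the text supports neither. What remains is the stated purpose. The objectives and research questions give the objective data one role, and it is not to test question 2.

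It can also be said that the Efficacy Outcomes section names no instrument, so an arm comparison of device data is not barred. That is true. But the questionnaires are identified elsewhere as the efficacy tools, and the planned 0-3, 3-6 and 6-12 month comparisons cannot use data that Study Assessments schedules at 0 and 6 months only. The table legend under Expected Duration of Participation suggests objective measures at every assessment, so those two places need reconciling.

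The bias sizes and SDs are assumed, and the pilot anchor is tiny. That stands too. The percentages show sensitivity and do not forecast this trial.

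The sub-sample is small, and the sleep and screen measures differ in kind: sleep hygiene against sleep duration, leisure screen time against social media use. Both points limit the remedy. Finally, the Budget section places the objective measures under a separate funding application, so their collection depends on that award.

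**Conclusion.** The point holds as a risk that could go undetected. A reader might go further and conclude that arm-dependent over-reporting will occur, or will certainly pass as a HELP effect. The documents do not support that. No bias is documented, and an overall mean-difference analysis would show a diluted signal.

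That youth will know their arm is inferred from the wait-list design and is not stated, but it is hard to avoid. Under the assumptions above, 10 to 15 min/day of extra over-reporting yields false lifestyle effects in about half to four-fifths of trials while overall alignment looks almost unchanged. The claims affected are secondary. The change is worth making because it uses data already planned.

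**What to change.** Amend Research Questions and Efficacy Outcomes as follows.

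1. Compare accelerometer activity, accelerometer sleep and phone social media use between the randomised arms at month 6, adjusted for month 0. Label these supportive outcomes for question 2 and report estimates with confidence intervals.
2. Report the question 6 alignment within each arm. For physical activity only, where both measures can be put in minutes per day, compare self-report change minus accelerometer change between arms. Do not use a standardised-scale discrepancy for any behaviour.

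Drawing the one-in-three sample within arm is optional, since a random draw is already balanced in expectation.

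The cost is analysis wording, with no new visits or data beyond those planned. The downside is imprecision: at best about 20 youth per arm at 122 complete, and fewer after invalid wear or lack of a smartphone. The text should say that a null result on either analysis does not show that reporting was unbiased.

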# Eligibility Criteria

## Inclusion Criteria

Participants will be eligible for this study if they are 12-17 years of age when they are seeking, waiting for or receiving support for emotional distress. To be included in the study, youth must be: a) able to provide informed consent to study participation, b) able to engage in the HELP e-intervention in English (French translation of the e-modules will not be available until intervention efficacy is established), c) willing to be randomized to a study group, d) willing to complete objective behaviour measures if selected (1 of 3 participants), e) willing to complete the study questionnaires, and f) willing to provide consent for evaluation of mental healthcare system outcomes via their health record.

## Exclusion Criteria

Youth will be excluded if they have an identified or suspected eating disorder because these youth often have a compulsive exercise co-morbidity that may be negatively impacted by the physical activity promoting components of the HELP e-resources. Youth will also be excluded if their health or family status is deemed to be inappropriate for the study as per their most responsible clinician.

# Study Design

This research will investigate the patient and healthcare system impacts of the HEalthy Lifestyle Project (HELP) e-intervention. The research design is a randomized, controlled trial comparing youth who immediately receive the intervention to youth randomized to receive the intervention 6-months later (wait list control). Efficacy outcomes will be assessed at 0, 3, 6 and 12 months. Healthcare system impacts will be extracted from medical records from 0 to 18 months.

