## Expected Duration of Participation

Youth will participate in the study for 12 months. All study visits and assessments are completed remotely. Youth can choose to complete the assessments via RedCAP survey or to have paper copies of the questionnaires sent by mail. The research coordinator will work virtually with each participant to support questionnaire completion. Completion of all questionnaires will require approximately 1 hour at each assessment timepoint. One of every three participants will be randomly selected to complete the objective behaviour measurements in addition to the questionnaires. Accelerometers will be distributed and collected by mail so that in-person visits to CHEO are not required. Participants selected for the objective measures will be required to wear an accelerometer on an elastic waistband 24 hours per day for 7 consecutive days. They will also be required to submit a screen shot of their social media screen time (app that already exists in smartphones) daily for the same 7 days. After the four assessment timepoints have been completed, youth will no longer be required to perform study activities but data collection on healthcare system impacts will continue to be collected via medical chart review for an additional 6 months. Participants randomized to the wait list control group will have access to the HELP e-intervention between the 6 and 12-month assessment timepoints.

| **Study Group** | **0 mos** | **0 to 3 mos** | **3 mos** | **3 to 6 mos** | **6 mos** | **6 to 12 mos** | **12 mos** | **12 to 18 mos** |
| --- | --- | --- | --- | --- | --- | --- | --- | --- |
| Intervention | Assess | HELP | Assess | HELP | Assess | ----- | Assess | Medical chart |
| Wait List Control | Assess | ----- | Assess | ----- | Assess | HELP | Assess | Medical chart |

Assess = completion of study questionnaires and objective measures (if applicable)
HELP = access to the HELP e-intervention with kinesiologist support
Medical chart = evaluation of mental health service use and inclusion of lifestyle behaviours in mental health service supports via medical chart review for 18 months from study enrollment

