# Statistical Plan

## Sample Size Determination

The size of the study sample will be determined by the number of eligible youth contacts (with 1Call1Click or directly to the research team). Our pilot study approached 5-10 youth/week via 1Call1Click with 25% enrolling, providing an expected 400-800 potential and ~100-200 enrolled participants over 18 recruitment months. Complete data for 122 youth would provide 80% power to detect a 3.4 point difference in emotional health (Strengths & Difficulties Questionnaire), equivalent to the 19.5% improvement observed in our 3-month pilot study.

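### Sustainability is read from one arm's month 6 to month 12 change, across opposite halves of the year, with no untreated comparator and no calendar term

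*Protocol*

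**What the plan says.** The Protocol's Study Design section sets the schedule: "Efficacy outcomes will be assessed at 0, 3, 6 and 12 months". Whether gains last six months after the intervention is the third Research Question, and it covers both emotional health and lifestyle behaviours. Efficacy Outcomes fixes how it is answered: "Differences between the 6 and 12-month assessments for youth randomized to immediate intervention access will evaluate the sustainability of the intervention effects". Expected Duration of Participation states what the other arm is doing at that time: "Participants randomized to the wait list control group will have access to the HELP e-intervention between the 6 and 12-month assessment timepoints".

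Efficacy Outcomes then names the covariates: "All models will be adjusted for age, gender, intervention adherence, type of mental health concern and support referral". Season, assessment date and school term appear neither there nor elsewhere in the statistical plan.

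The same section prescribes paired t-tests of enrolment against month 6 for stage of change, and extends them to behaviour: "The same analyses will be completed for each behaviour outcome with stage of change at 6-months a mandatory variable". Sample Size Determination expects "100-200 enrolled participants over 18 recruitment months".

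**The concern.** Two assessments six months apart fall in opposite halves of the year for every participant. Physical activity, sleep and leisure screen time at 12 to 17 years plausibly differ between those halves. A before-and-after change over six months in one arm therefore mixes what happened to the youth with what happened to the season. After month 6 there is no untreated group from which the seasonal part could be subtracted.

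At stake is the answer to the sustainability question for the lifestyle outcomes. A change that was fully kept could look partly lost, or a lost change could look kept, because of the months in which recruitment opened and closed. Paired tests of enrolment against month 6 have the same weakness, since they use no control group and span the same half-year.

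**Working it through.** **Inputs from the Protocol.** Visits at 0, 3, 6 and 12 months; 18 months of recruitment; complete data for 122 youth; significance at 0.05. **Assumptions.** 1:1 allocation, two-sided tests, even accrual, and a yearly pattern with peak-to-trough swing S. The documents give no S and no SD for any lifestyle outcome, so results are shown over a range.

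**The plan's own figure.** The 122 cannot be reproduced, because no SD is stated. With 61 per arm, 80% power for 3.4 points requires 3.4/SD = (1.960 + 0.842) × √(2/61) = 0.507, so SD = 6.70. This does not bear on the season question. Only n = 61 is carried forward.

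**Seasonal part of one youth's change.** Let the season effect at calendar month t be (S/2)·cos(2πt/12 − φ). For a youth enrolled at t, month 12 minus month 6 gives (S/2)[cos x − cos(x + π)] = S·cos x, with x = 2πt/12 − φ. Month 12 minus month 0 gives exactly zero.

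**Average over 18 months of even enrolment.** Twelve of the 18 months cancel. The other six contribute at most (S/18) × (12/π) = 2S/(3π) = 0.212·S, and zero at the most favourable start month. If the year is two flat halves, the maximum is (6/18)·S = 0.333·S. The same limits apply to a within-arm change from month 0 to month 6.

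**Effect on a test of a fully sustained change.** Measure S in SDs of the six-month change with season removed. The variance of the change is then V = 1 + S²/2 (sine) or 1 + S² (two halves), and the standard error is √(V/61). At the worst start month, by normal approximation:

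| S | Sine: residue | Sine: residue/SE | Sine: rejects | Halves: residue | Halves: residue/SE | Halves: rejects |
|---|---|---|---|---|---|---|
| 0.25 | 0.053 | 0.41 | 7% | 0.083 | 0.63 | 10% |
| 0.5 | 0.106 | 0.78 | 12% | 0.167 | 1.16 | 21% |
| 1 | 0.212 | 1.35 | 27% | 0.333 | 1.84 | 45% |

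At the best start month every entry is 5%. Averaged over start months, the sine figures are about 6%, 9% and 16%. A simulated one-sample t-test (20,000 runs, worst start month) gave 12.3% at S = 0.5 and 26.5% at S = 1, in agreement with the table.

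**The randomised contrast.** From month 0 to month 6 both arms are followed over the same calendar, so the seasonal part cancels in expectation. It stays in the variance, with share (S²/2)/(1 + S²/2) = 3%, 11% and 33% for S = 0.25, 0.5 and 1 (sine). A calendar term could recover some of that.

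**The case against.** **The calendar effect is only partial.** A reader might infer that sustainability is wholly confounded with season. It is not: even 18-month accrual removes at least two thirds of the swing from the mean, and a favourable start month removes all of it. School term does not reliably alternate either, since October and April are six months apart and both normally fall in term. This stands. Uneven enrolment could leave more than the limits shown, and the Protocol lets enrolment follow the flow of youth contacts.

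**The size is assumed.** Nothing in the documents shows that these outcomes are seasonal, and the highest rejection rates belong to the worst start month. This also stands, so the results are given as ranges that start at 5%.

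**The main comparison is protected.** A reader might infer that the randomised lifestyle comparison is biased or loses planned power. The documents support neither. The wait-list arm shares the calendar up to month 6, and Sample Size Determination claims power only for the Strengths and Difficulties Questionnaire. An SD of observed change would already contain the seasonal variance. For that contrast, season adjustment is an optional gain in precision.

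**This may be settled in an analysis plan not shown.** That is fair for a precision covariate. It is weaker here, because the Protocol itself fixes the within-arm sustainability contrast and names the covariates for all models.

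**The plan uses a repeated measures model, not a one-sample test.** True, and the rejection rates are approximate for that reason. Without a calendar term, though, the within-arm month 6 to month 12 contrast in such a model still carries the seasonal residue.

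**Conclusion.** The point holds for the uncontrolled within-arm contrasts: the sustainability reading above all, and the paired behaviour tests of enrolment against month 6. As written, the sustainability contrast can absorb part of a half-year season shift, and nothing in the named models removes it.

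The size depends on an assumed swing. The residue is 0 to 0.21·S for a sine pattern, or 0 to 0.33·S for two flat halves. With 61 youth and a sine pattern, false rejection of a fully sustained effect runs from 5% to at most about 7%, 12% and 27% at S = 0.25, 0.5 and 1 SD of the change net of season. These figures rest on even accrual over 18 months and 1:1 allocation. The visit schedule is not itself an error, and the randomised month 0 to month 6 comparison, including the primary outcome, is not biased by season.

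**What to change.** In Efficacy Outcomes, make two changes.

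1. Add a calendar term at each assessment to the repeated measures models, either sine and cosine of the assessment date or a season factor, estimated from both arms and all visits. Enrolment is staggered over 18 months, so calendar time can be separated from time in study.
2. For sustainability, report the immediate arm's month 0 to month 12 change beside the month 6 to month 12 difference. The first is season-matched and uses questionnaires already scheduled. It answers a slightly different question, net change from baseline, so it belongs beside the planned contrast and does not replace it.

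The season-matched pair may not exist for the objective measures: Study Assessments places the "accelerometer to wear for 7 days at the time of the 0 and 6-month assessments", whereas the table notes in Expected Duration of Participation include objective measures at every assessment. The two sections should be reconciled.

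The cost is wording and one or two degrees of freedom, with no new visits. A calendar term does not supply a control group: the sustainability contrast stays open to maturation and to other services used meanwhile, and the Protocol should describe it as uncontrolled.
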